## Outcomes

### Primary outcome measurement

The primary outcome will be measured by changes in the Eczema Area and Severity Index (EASI) before and after 3 weeks’ application of experimental medications. Key signs of eczema, including erythema (E), infiltration/population (I), excoriation (Ex), and lichenification (L), will be assessed on a numeric scale of 0 to 3. Then, the percentage of area involved for each of the four body regions will be assigned a proportional score from 0 to 6: 0 = no eruption; 1 = <10%; 2 = <10–29%; 3 = <30–49%; 4 = <50–69%; 5 = <70–89%; and 6 = >90–100%. Finally, an established multiplier based on the age of the patient will be used. Please refer to the following formula for patients over 8 years of age. The multiplier for patients under 8 years of age is indicated in parentheses and in italics:

Upper Limbs [(E + I + Ex + L) × Area × 0.2 (*0.2*)] + Lower Limbs [(E + I + Ex + L) × Area × 0.4 (*0.3*)] + Trunk Limbs [(E + I + Ex + L) × Area × 0.3 (*0.3*)] + Head/Neck [(E + I + Ex + L) × Area × 0.1 (*0.2*)] [11].

### Secondary outcome measurements

Secondary outcome measurements will include SCORAD score [12], transepidermal water loss (TEWL) using TM 300 [13], the Dermatology Life Quality Index (DLQI) [14], total IgE, eosinophil count, and interleukin (IL)-17, IL-22, and interferon (IFN)-γ [15]. These parameters will be measured before and after 3 weeks’ application of experimental medications. The consumption of orally administered antihistamines and usage of emollients, lotions, and ointments that do not contain GCs during the study will be checked.

### Safety outcome measurements

Prior to randomization and immediately after treatment completion, we will perform the following tests on all participants: CBC D/C, AST/ALT, BUN/Cr, ESR, and vital signs. These tests will serve to exclude participants who have serious illnesses or abnormal liver, kidney, or other organ function. Additionally, subjective dermal tolerability assessment and the Draize score will be assessed after completion of the study [16].

Listed adverse events verified by the KFDA for *Jaungo* include allergic skin reactions including rash and pruritus. Investigators will assess the incidence and intensity of adverse events. In addition, a causality evaluation of adverse drug reactions will be discussed and documented in Case Report Forms.

### Sample size

This study aims to investigate the efficacy, safety, and dose response for the approved drug, *Jaungo*, with a new indication. *Jaungo* is already approved for use in xerosis cutis, frostbite, miliaria, anal fissures, and rhus dermatitis. There are no previous clinical trials of the use of *Jaungo* in AD. Following the study by Julious [17], we considered the practical feasibility, the possible expectation of the mean and standard deviation, regulations of the KFDA, and risks which fail to detect the difference among the study groups to determine sample size. From this, we decided that 12 patients per group were needed.

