## Methods

### Study setting and design overview

This study will be conducted at the Kyung Hee University Korean Medicine Hospital in Seoul, Korea. The study is designed as a randomized, double-blind, placebo-controlled, single-center, phase IIa clinical trial to investigate the safety, preliminary efficacy, and dose response of *Jaungo* for treatment of AD. The study aims to enroll 34 patients with AD. Participants fulfilling the eligibility criteria will be selected and randomly distributed into three parallel groups: treatment 1, treatment 2, and the placebo group. Treatment group 1 applies *Jaungo* twice a day; treatment group 2 applies *Jaungo* and placebo ointments once a day, separately; and the placebo group applies placebo ointment twice a day, for a total of 3 weeks each. Participants will be evaluated for AD before and after applying ointment (see Figs. 1 and 2). A completed Standard Protocol Items: Recommendations for Interventional Trials (SPIRIT) Checklist for the trial is available (see Additional file 1).

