### Randomization and allocation

Before assigning randomization, all participants will be informed that they will be distributed into one of three groups. Thirty-four participants will be randomized into three groups in a 1:1:1 ratio, using block randomization with a block size of 3 or 6, where 11–12 participants are planned for each group. Randomization distribution will occur on the second visit to the clinical research center. Participants will be assigned random numbers via a web-based random number generator system developed by an independent expert on web programming using Django Web Framework (https://www.djangoproject.com). The clinical pharmacy will be supplied with the experimental and placebo ointments in identical containers labeled with random numbers, which correspond to the participant’s assigned number, and “for morning use” or “for evening use.” The participant’s randomly assigned number will dictate which ointments the clinical pharmacist will supply to them.

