### Statistical analysis

The primary hypothesis is that topical application of *Jaungo* is more effective than the placebo ointment for treating AD. Baseline data collected on each participant at randomization in the trial will be used to describe the population of patients, assess comparability of treatment groups, achieve balanced randomization, adjust for possible confounding prognostic factors, and undertake subgroup analyses. The baseline characteristics of the three groups, including sex, age, duration of AD, total IgE level, and SCORAD score will be compared. Analysis of variance (ANOVA) will be used to investigate differences in continuously scaled variables, and chi-squared tests will be used to identify significant variations in proportions across treatment groups.

We will also compare the efficacy of *Jaungo* and placebo ointments based on the change in primary outcome, or EASI score, from day 0 to the end of the study period (3 weeks). Mean differences in the EASI score from baseline value to the end of treatment will be compared using ANOVA among the three groups. A paired Student’s *t* test will be used to compare the mean change within a group. Secondary outcomes (SCORAD score, TEWL, DLQI, total IgE, eosinophil count, IL-17, IL-22, and IFN-γ) will also be utilized to compare the efficacy of *Jaungo* and placebo ointments in the same manner as the primary outcome/EASI score. To evaluate safety, the Draize score and adverse events will be presented in a descriptive manner.

Analyses will be performed for two populations: (1) an intention-to-treat population consisting of all randomized participants who have at least one measurable outcome to report following treatment (missing data are replaced with the last observation values) and (2) a per-protocol population including only participants without major protocol deviations. All data will be descriptively analyzed. All main analyses will be based on the intention-to-treat population and conducted using the last observation carried forward imputation method. Statistical analyses will be conducted in a blind manner by an independent statistician and performed using the SPSS 21 (IBM Inc., Armonk, NY, USA), where the level of significance is established at *α* = 0.05.

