## Discussion

AD is an eczematous disorder that manifests with erythema, microvesiculation, exudation and crusting in its acute phase, and dry, red, scaly skin in its chronic phase [3]. Treatment guidelines for AD focus on the acute stage of the disease which includes emollients and topical GCs. Topical GCs are the mainstay treatment for AD flare-ups, and in many cases AD can be controlled with topical corticosteroids or topical calcineurin inhibitors; however, some chronic AD patients require other treatment options due to GC side effects.

*Jaungo* is an approved herbal ointment for xerosis cutis, frostbite, miliaria, anal fissures, and rhus dermatitis in Korea. Topical application of *Jaungo* was found to have anti-inflammatory and antiallergic activity in our previous in-vivo and in-vitro studies [5–7]. Based on these findings, we designed a phase IIa clinical study to determine the clinical efficacy of *Jaungo* and its possible treatment mechanism in chronic-stage AD. This preliminary and exploratory study is critical for future confirmatory clinical trials, as no information exists for *Jaungo*’s application dose, frequency, and length of time that it should be administered in AD.

One of the important issues that we had to consider in this study was the blindness between the experimental drug, *Jaungo*, and the placebo ointment. *Jaungo* has a unique color and aroma. The characteristic red color is due to the *Lithospermi* radix, and its distinctive aroma is due to the flavor components of bees wax and *Angelica gigantis* radix. Red iron oxide and ginseng-flavored extract were used to manufacture the placebo ointment. Substances, composition, and manufacturing methods of the placebo ointment were approved by the KFDA. Additionally, to conceal the distribution data from researchers and participants, a web-based random number generator system was developed by an independent expert on web programming using Django Web Framework.

Limitations of this study are that it involves only 34 participants in a single center. This could potentially influence the generalizability of the study results. However, this study was designed to find the most responsive AD symptoms, to establish the proper application dose and frequency of *Jaungo*, and to identify the possible mechanism of action utilized by *Jaungo* for further study. In conclusion, this exploratory study will contribute to establishing *Jaungo*’s efficacy, safety, and dose response in AD.

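### The sample-size section calls for 12 patients per group (36 in all), but the trial enrols and randomises 34, so no allocation can give 12 in every arm; a small but plain inconsistency to reconcile

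*Protocol article*

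**What the plan says.** The protocol article gives the size of the trial in two ways.

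- **Sample size:** "From this, we decided that 12 patients per group were needed". The reasons listed are practical feasibility, what might be expected for the mean and standard deviation, regulatory requirements and the risk of missing a difference. No effect size, standard deviation or power is given.
- **Study setting and design overview:** "The study aims to enroll 34 patients with AD". The abstract gives the same total.
- **Randomization and allocation:** "Thirty-four participants will be randomized into three groups in a 1:1:1 ratio", and then "using block randomization with a block size of 3 or 6, where 11–12 participants are planned for each group".
- **Discussion:** "Limitations of this study are that it involves only 34 participants in a single center".

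The article does not say whether block sizes 3 and 6 are mixed in one list, in what proportion, or how the list ends.

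**The concern.** The sample-size section says how many patients are needed, and the randomisation section describes a design that cannot supply them. This is a conflict between two printed figures, not a detail left to a fuller document. A reader cannot tell which size was intended, and whoever reports the trial will have to choose one of them as the planned number.

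A second, smaller matter follows from the total. Because 34 is a multiple of neither 3 nor 6, the last block is always cut short. Depending on which block is cut, the scheme may not keep to its own range of 11 to 12 per group.

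**Working it through.** **Inputs.** 12 per group (Sample size); three groups, 34 randomised 1:1:1, blocks of 3 or 6, 11 to 12 per group (Randomization and allocation); significance level 0.05 (Statistical analysis), taken here as two-sided because the article does not say. The 12 is a judgement figure, so no formula can reproduce it. What can be checked is whether the stated figures agree.

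**1. Totals.** 3 × 12 = 36. The shortfall is 36 − 34 = 2, or 2/36 = 5.6%. The average arm is 34/3 = 11.33, so at least one arm is below 12 before any patient is lost. The range of 11 to 12 does fit 34, as 12 + 11 + 11.

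**2. Arm sizes with 34 from permuted blocks.**

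- Blocks of 3 only: eleven full blocks use 33 patients (11 each) and the 34th adds one. The result is always 12/11/11.
- Blocks of 6 only: five full blocks use 30 (10 each), and four of the six slots of the last block are used. There are C(6,4) = 15 sets of four slots. In 3 of them one arm is left out, giving 2/2/0; in the other 12 the split is 2/1/1. So 12/12/10 has probability 3/15 = 1/5, and 12/11/11 has 4/5.
- Sizes drawn at random, 3 and 6 equally likely (an assumption): a block ends at position 30 with probability 0.667 and the next block is of size 6 with probability 0.5. The chance of 12/12/10 is 0.667 × 0.5 × 0.2 = 0.067.

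The chance of an arm of 10 is therefore 0% with blocks of 3, about 6.7% with the assumed equal mix, and 20% with blocks of 6.

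**3. What two patients are worth.** The 95% half-width for a pairwise difference, in SD units and with pooled error degrees of freedom N − 3, is t × √(1/n₁ + 1/n₂).

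| Arms compared | N | t | √(1/n₁ + 1/n₂) | Half-width (SD) |
|---|---|---|---|---|
| 12 v 12 | 36 | 2.035 | 0.408 | 0.83 |
| 12 v 11 | 34 | 2.040 | 0.417 | 0.85 |
| 11 v 11 | 34 | 2.040 | 0.426 | 0.87 |
| 12 v 10 | 34 | 2.040 | 0.428 | 0.87 |

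As an illustration only, suppose there were 80% power at 12 per arm, which the article does not claim. A pairwise t test would then have 78.1% (12 v 11), 76.1% (11 v 11) or 75.8% (12 v 10). A three-group ANOVA with equally spaced means would have 77.9% at 12/11/11 when an extreme arm holds the 12, and 75.7% when an extreme arm has 10. The loss in these cases is about 2 to 4 points.

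**4. Would 36 close the blocks?** Yes with blocks of 3 only or of 6 only, since 36 is a multiple of both. Not automatically with a random mix. With equal chances, a block ends at position 33 with probability 0.667 and is followed by a block of 6 with probability 0.5, so about one list in three is still open at 36. Of the C(6,3) = 20 sets of three slots in that open block, 12 are uneven (2/1/0). That gives 13/12/11 in about 0.333 × 12/20 = 20% of lists.

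**The case against.** The best defence is that little depends on the gap. The 12 does not come from a power calculation, so two patients fewer break no stated power or precision. The randomisation section is open about 11 to 12 per group, and the discussion names the total of 34 as a limitation and describes the study as preliminary and exploratory. All of this stands and sets the severity. It does not remove the conflict: 3 × 12 is exact, the section speaks of what was needed, and no passage says that 12 was a rounded or upper figure.

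It can also be said that the arm of 10 depends on how the list was built, which a condensed article may leave to the full protocol. That too stands. The arm of 10 is a conditional possibility, and with blocks of 3 it cannot occur.

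Three stronger readings are tempting but not supported:

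- **The trial falls short of its power.** No power is stated, and the power losses above rest on an assumed 80%.
- **The lack of a dropout allowance is an error.** No dropout rate is given, and the article does not say whether 12 means randomised or evaluable patients. A condensed article can leave this out.
- **The size contradicts the abstract's statement that the study will determine efficacy.** This is a matter of wording, and the conclusion of the discussion is milder. Pairwise interval widths also do not describe the planned three-group ANOVA directly, and they differ by only 0.04 SD between 12 and 11 per arm.

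**Conclusion.** The inconsistency is real and needs no assumption: the sample-size section implies 36, every stated total is 34, and no split of 34 puts 12 in all three arms. The allocation scheme as described also does not guarantee 11 to 12 per group. If a block of 6 covers positions 31 to 36, an arm of 10 results one time in five; across possible block mixes the chance is 0 to 20%, and the 6.7% figure holds only for an assumed equal mix.

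The consequence is small. The half-width for a pairwise difference widens from about 0.83 to 0.87 SD, assuming a common SD and two-sided 95% intervals. This is a low-severity correction of a stated figure and does not threaten the conclusions of an exploratory trial.

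**What to change.** Bring the Sample size section into line with Randomization and allocation: state that 34 patients will be randomised, 11 to 12 per group, that the number was chosen on grounds of feasibility, and that no power is claimed. This costs one or two sentences.

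Make the allocation list end with blocks of 3, so that a block closes at position 33 and 12/11/11 is certain. Enrolment has begun, so the list may already exist. In that case the clinical research organisation that holds it can check the closing blocks without disclosing anything to blinded staff. If a block of 6 does cover positions 31 to 36, the text should give the range as 10 to 12.

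If the sponsor in fact intended 36, correct 34 wherever it appears and fix the block sequence so that it closes at exactly 36; changing the total alone does not secure 12 per arm if the sizes are mixed at random. This route costs two more patients and, as the protocol has been approved and enrolment has started, probably a formal amendment. Rewording is the cheaper route and is enough to resolve the point.

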### Recruitment

Participants will be recruited by bulletin board advertisements and the online homepages of Kyung Hee University Korean Medicine Hospital, Kyung Hee University Hospital at Gangdong, and Kyung Hee University in Seoul, Korea. Respondents will be contacted by clinical trial coordinators to determine their eligibility via a telephone prescreening. If an applicant meets the study criteria, they will be invited to the clinical research center to be examined for eligibility.

### Randomization and allocation

Before assigning randomization, all participants will be informed that they will be distributed into one of three groups. Thirty-four participants will be randomized into three groups in a 1:1:1 ratio, using block randomization with a block size of 3 or 6, where 11–12 participants are planned for each group. Randomization distribution will occur on the second visit to the clinical research center. Participants will be assigned random numbers via a web-based random number generator system developed by an independent expert on web programming using Django Web Framework (https://www.djangoproject.com). The clinical pharmacy will be supplied with the experimental and placebo ointments in identical containers labeled with random numbers, which correspond to the participant’s assigned number, and “for morning use” or “for evening use.” The participant’s randomly assigned number will dictate which ointments the clinical pharmacist will supply to them.

### Blinding

To ensure blinding, a matched placebo ointment identical in color, texture, weight, and odor will be utilized and stored in a container identical to that of *Jaungo*. The *Jaungo* and placebo ointments will be labeled with a random number and “for morning use” or “for evening use” in an identical form. Treatment group 1 will receive two containers of *Jaungo*, one labeled with “for morning use” and the other “for evening use,” treatment group 2 will receive one container of *Jaungo* and one container of placebo ointment where one of the containers is labeled with “for morning use” and the other “for evening use.” The placebo group will receive two containers of placebo ointment, one labeled with “for morning use” and the other “for evening use.” The clinical pharmacist will supply *Jaungo*, the placebo ointment, or both to the patient depending on the patient’s assigned number. If the ointments are lost or destroyed, the clinical pharmacist will supply the patient with extra ointment labeled in an identical manner to maintain blinding.

In this trial, treatment distribution will remain unknown to the participants, investigators, outcomes assessors, statistician, and other staff until the end of the study. The randomization list and blinding codes will be kept strictly confidential. Access to the randomization list will be limited to the Clinical Research Organization (CRO) staff and the list will only be opened as a standard operating procedure. In the event that the randomization list has to be opened immediately, owing to an urgent situation pertaining to serious adverse events, the primary investigator must report the incident to the CRO. Participants will remain blinded to their respective treatment group until the final visit of the last randomized participant. The success of blinding will be assessed at each participant’s final visit. Researchers who are blinded to the distribution data will perform the outcome assessment. The blinding procedure will also be verified by the authorized CRO.

### Data collection, management, quality control and monitoring

To maintain the quality of this trial, monitoring and data management including data collection, validation, and completion will be conducted by the Institute of Safety and Effectiveness Evaluation for Korean Medicine (ISEE), a CRO located in Seoul, Korea. To ensure that outcome assessments are of a high standard in accordance with the trial protocol, the investigator and the assistants will attend a 6-h training workshop prior to the initiation of the trial. The investigator and the assistants will also be provided with a written protocol and standard operating procedure documents. All the data will be checked regularly by clinical trial coordinators from ISEE.

### Statistical analysis

The primary hypothesis is that topical application of *Jaungo* is more effective than the placebo ointment for treating AD. Baseline data collected on each participant at randomization in the trial will be used to describe the population of patients, assess comparability of treatment groups, achieve balanced randomization, adjust for possible confounding prognostic factors, and undertake subgroup analyses. The baseline characteristics of the three groups, including sex, age, duration of AD, total IgE level, and SCORAD score will be compared. Analysis of variance (ANOVA) will be used to investigate differences in continuously scaled variables, and chi-squared tests will be used to identify significant variations in proportions across treatment groups.

We will also compare the efficacy of *Jaungo* and placebo ointments based on the change in primary outcome, or EASI score, from day 0 to the end of the study period (3 weeks). Mean differences in the EASI score from baseline value to the end of treatment will be compared using ANOVA among the three groups. A paired Student’s *t* test will be used to compare the mean change within a group. Secondary outcomes (SCORAD score, TEWL, DLQI, total IgE, eosinophil count, IL-17, IL-22, and IFN-γ) will also be utilized to compare the efficacy of *Jaungo* and placebo ointments in the same manner as the primary outcome/EASI score. To evaluate safety, the Draize score and adverse events will be presented in a descriptive manner.

Analyses will be performed for two populations: (1) an intention-to-treat population consisting of all randomized participants who have at least one measurable outcome to report following treatment (missing data are replaced with the last observation values) and (2) a per-protocol population including only participants without major protocol deviations. All data will be descriptively analyzed. All main analyses will be based on the intention-to-treat population and conducted using the last observation carried forward imputation method. Statistical analyses will be conducted in a blind manner by an independent statistician and performed using the SPSS 21 (IBM Inc., Armonk, NY, USA), where the level of significance is established at *α* = 0.05.

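### Change in EASI and in every secondary outcome is compared without a baseline term although baseline is measured: a valid test that gives away precision

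*Protocol article*

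**What the plan says.** All of this is in the protocol article.

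- Statistical analysis, hypothesis: "topical application of *Jaungo* is more effective than the placebo ointment for treating AD".
- Statistical analysis, primary variable: "the change in primary outcome, or EASI score, from day 0 to the end of the study period (3 weeks".
- Statistical analysis, primary test: "Mean differences in the EASI score from baseline value to the end of treatment will be compared using ANOVA among the three groups". No covariate is named. Paired t tests are added within groups.
- Statistical analysis, secondary outcomes: SCORAD, TEWL, DLQI, total IgE, eosinophil count, IL-17, IL-22 and IFN-γ are analysed "in the same manner as the primary outcome/EASI score". No transformation or rank method is named.
- Statistical analysis, uses of baseline data: among others, to "adjust for possible confounding prognostic factors, and undertake subgroup analyses". This is tied to no model, covariate or outcome. The characteristics named for the baseline comparison do not include EASI.
- Secondary outcome measurements: "These parameters will be measured before and after 3 weeks". The primary outcome is also a before-and-after change, so a baseline value exists for every efficacy outcome.
- Sample size: "we decided that 12 patients per group were needed". Randomization and allocation plans 34 participants, 11 to 12 per group.

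**The concern.** The named test uses baseline only by subtracting it. Subtraction fixes the coefficient of baseline at 1. Where the true regression slope of week 3 on baseline is below 1, it over-corrects and adds noise. ANCOVA estimates the slope instead. With 11 to 12 per group the trial can detect only large effects, so wasted precision is costly.

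The section also sits badly with itself. It announces adjustment for prognostic factors and then names an unadjusted test, so a reader cannot tell whether the main result is adjusted. If it is, the covariates could be chosen after the baseline comparisons have been seen.

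The same raw-change ANOVA goes to the laboratory markers. The Discussion gives identifying a possible mechanism as one aim of the study. If those markers are strongly right-skewed, a few high values dominate the variance of raw change, and a null result could be misread as no effect on the mechanism.

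**Working it through.** **The plan's own figure.** The 12 per group cannot be reproduced, because the Sample size section gives no effect size, SD or power. For orientation, with two-sided α = 0.05 (sidedness is not stated) and 80% power, the detectable pairwise difference is √(2/n) × (1.96 + 0.84). That is 1.19 SD of change at n = 11 and 1.14 at n = 12, or 1.26 and 1.20 by noncentral t.

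**Inputs for EASI.** From the article: N = 34, three groups, change from baseline to week 3. Assumed, because not stated: baseline to week-3 correlation r from 0.3 to 0.9, and week-3 SD equal to k times baseline SD.

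**Formulas**, in units of baseline variance:
- raw change: 1 + k² − 2rk, which is 2(1 − r) at k = 1
- ANCOVA: k²(1 − r²), which is 1 − r² at k = 1
- ratio at k = 1: (1 + r)/2
- cost of estimating one slope: multiply by 1 + 1/(34 − 3 − 2) = 1 + 1/29 ≈ 1.034

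**Results, equal SDs (k = 1), slope cost included:**

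| r | (1 + r)/2 | ratio with slope cost | variance saved | patients raw change needs to match ANCOVA at 34 | ANCOVA power where raw change has 80% |
|---|---|---|---|---|---|
| 0.3 | 0.65 | 0.67 | 33% | 51 | 93% |
| 0.5 | 0.75 | 0.78 | 22% | 44 | 89% |
| 0.7 | 0.85 | 0.88 | 12% | 39 | 85% |
| 0.9 | 0.95 | 0.98 | 2% | 35 | 81% |

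**Unequal SDs, slope cost included:**
- k = 0.8: ratios 0.52, 0.59, 0.65 and 0.63 at r = 0.3, 0.5, 0.7 and 0.9.
- k = 1.2, r = 0.5: 1.44 × 0.75 / (2.44 − 1.20) = 1.08/1.24 = 0.87, and × 1.034 = 0.90.
- k = 1.2, r = 0.7: 1.44 × 0.51 / (2.44 − 1.68) = 0.734/0.76 = 0.97, and × 1.034 = 1.00, so no gain.

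**Baseline imbalance.** With 12 and 11 in two groups, the SD of the chance baseline difference is √(1/12 + 1/11) = 0.42 SD. At k = 1, raw change leaves (1 − r) of it as error, 0.21 SD at r = 0.5. The excess variance of raw change over ANCOVA is proportional to 2(1 − r) − (1 − r²) = (1 − r)². At r = 0.5 this is (1/12 + 1/11) × 0.25 = 0.044 = 0.21². The imbalance is therefore the same quantity as the precision loss, not a further one.

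**Laboratory markers.** Their distribution is not described. Assumed: log-normal; the same log SD at both visits; a log effect of −0.7 in the top group (e^−0.7 ≈ 0.50, about a halving) and half that on the log scale in the middle group; groups of 12/11/11. There were 3000 simulated trials per cell, each testing the three-group difference at 0.05.

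| SD of log | r | raw-change ANOVA | log-scale ANCOVA |
|---|---|---|---|
| 0.5 | 0.7 | 73% | 98% |
| 0.5 | 0.9 | 98% | 100% |
| 1.0 | 0.7 | 15% | 48% |
| 1.0 | 0.9 | 37% | 91% |
| 1.5 | 0.7 | 5% | 24% |
| 1.5 | 0.9 | 11% | 55% |

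With no effect, raw-change ANOVA rejected in about 2% to 5% of trials and log-scale ANCOVA in about 5% to 6%.

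**The case against.** The planned test is not an error. Under randomization a comparison of mean change is unbiased, and the simulation shows no excess of false positives. The trial is phase IIa, calls itself exploratory and states no power, so no promise is broken. This stands, and it limits the point to efficiency.

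The article does mention adjustment, and the choice of covariates is commonly left to a SAP, which is not shown. This stands in part. The point is not that covariate detail is missing. It is that the article names a test for the primary and all secondary outcomes, and that test does not carry out the adjustment announced in the same section.

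The gain depends on quantities the article does not give. At r = 0.9 with equal SDs it is about 2%, and it vanishes at r = 0.7 if the week-3 SD is 1.2 times the baseline SD. The cap on objective SCORAD at entry might narrow baseline spread and push in that direction. This stands, and is why a range is shown.

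For the laboratory markers, neither skewness nor a halving in three weeks is documented. At log SD 0.5 the raw test does well, and at log SD 1.5 with r = 0.7 even the log-scale model reaches only 24%. At r = 0.9, baseline adjustment by itself is worth little (about 2% of variance at equal SDs), so most of the gain there must come from the log scale. A log analysis also needs a rule for zeros and undetectable values. All of this stands, and makes this part conditional.

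**Conclusion.** The point holds as a nearly free gain in precision. The article fixes an unadjusted comparison of raw change for every efficacy outcome although a baseline value exists for each. With equal SDs and N = 34, adjusting for baseline saves about 33%, 22%, 12% and 2% of the variance of a treatment contrast at r = 0.3, 0.5, 0.7 and 0.9. It saves more if the week-3 SD is smaller than the baseline SD, and less or nothing if it is larger.

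Three stronger conclusions that a reader might draw are not supported:
- That the planned test is biased or inflates false positives: it does neither.
- That baseline imbalance is a second harm on top of lost precision: algebraically it is the same one.
- That the test of the laboratory markers is known to have little power: this depends on skewness and an effect size that the article does not state. Under the assumptions above, the gain runs from small (98% to 100%) to large (37% to 91%).

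**What to change.** - Analyse week-3 EASI by ANCOVA with treatment group and baseline EASI, and name baseline EASI now as the prespecified covariate.
- Use the same form for each secondary outcome, with its own baseline as covariate.
- State that covariates are not selected from the baseline comparisons, and reword the sentence on adjustment so that it points to this model.
- For total IgE, eosinophil count, IL-17, IL-22 and IFN-γ, prespecify ANCOVA of log week-3 value on log baseline, report geometric mean ratios, and fix a rule for zero or below-detection values before unblinding.

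The cost is one degree of freedom per model, a detection-limit rule and changed analysis wording. No new data are needed. The article reports the trial as ongoing, with the statistician blinded to allocation until the end, so the change can be made without knowledge of the results.
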